### Study population

#### Patients

To be eligible for recruitment into the study patients must be aged 18 years or older; have reached stage 5 chronic kidney disease with estimated glomerular filtration rate ≤15 mL/min/1.73m^2^as measured by the MDRD formula [20]; and have made a confirmed decision for conservative kidney management, i.e. management without dialysis or other renal replacement therapy. Patients lacking capacity to give consent to participate will be excluded. Capacity for consent to participate will be assessed in collaboration with the supervising nephrologists. Non-English speaking patients or those who do not adequately understand verbal or written information will be excluded.

#### Carers

To be eligible for recruitment into the study participants must identify as the primary carer for the patient who has made a confirmed decision for conservative kidney management. They must be over 18 years and the patient must agree that the carer can be approached to participate. Carers can only participate in the study if they ‘opt in’ to study by making contact with the Research Nurse. Carers who lack capacity to give consent to participate in the study will be excluded. Non-English speaking carers will also be excluded.

#### Renal physicians/clinical nurse specialists

Renal physicians and clinical nurse specialists (CNS) recruited to the study must have experience of managing clinical consultations with patients who have stage 5 chronic kidney disease and are opting for conservative kidney management. Those clinicians and nurses without experience of managing consultations with patients who opt for conservative kidney management and who are not nephrologists or renal nurses will be excluded.

### Recruitment

#### Patients

Recruitment will take place over 18 months and data collection will continue for another 12 months or until death. The initial treatment decision is made in clinic with a renal physician or a CNS. Once the decision is made Research Nurses at each site will liaise with renal physicians or CNS and use the inclusion/exclusion criteria to identify potential participants. All patients across the ten study sites who have made a decision not to initiate dialysis and meet the study inclusion criteria will be sent written information about the study (see Fig. 1). They will be contacted to see if they are willing to take part in the study. If willing to participate written informed consent will be obtained at their next clinic visit (Baseline). This should take place within 3 months after the initial decision not to embark on dialysis.

**Fig. 1 Fig1:**
[figure not shown]
CONSORT diagram showing the flow of participants through each stage of study

If patients wish they can complete questionnaires themselves, with the nurses or with their carers. The way in which the data are captured (self-completion or help from staff member or carer) will be noted on the front sheet of the questionnaires.

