#### Carers

With the patient’s agreement, and if the patient is happy for the carer to participate in the study, information will be sent to the patient to give to their carer. Carers will be asked to contact the Research Nurse if they are interested in ‘opting-in’ to the study. If a carer is interested in participating they will be invited to attend the patient’s next clinic appointment so that informed consent can be obtained and baseline data collected (see Fig. 1). If the carer is unable to attend this clinic visit then the Research Nurse will send a consent form and baseline data collection tools to their home. The carers will be asked to return the consent form to the hospital. Information on how to complete the tools will be given over the telephone. Carers can either complete the tools themselves or with the assistance of a Research Nurse.

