#### Sample size

The primary outcome is to measure the true mean QOL at 3 months using the EQ-5D-5L Visual Analogue Scale (EQ-VAS). The EQ-VAS asks patients to place their health on an interval scale from 0–100 where 0 is the worst state they can imagine and 100 is the best. Using a standard deviation estimate of 18 from a similar study (Nephrol Dial Transplant (2004) 19: 1594–1599),with 100 individuals in our sample we would calculate a 95 % confidence interval for the true mean which would be of width 7.2 units, i.e. 95 % of the time we would estimate the true mean within plus or minus 3.6 units. With an estimated death/dropout rate at 3 months of 10 %, a total of 112 patients are required. For the exploratory qualitative interviews with nephrologists and CNS, in order to achieve data saturation when no new patterns emerge, a sample of approximately 15–20 will be recruited until data saturation reached [39].

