**Tools for use with patient**
*Kidney Disease QOL-36™* Quality of life of patients will be measured using the Kidney Disease QOL-36™ Survey (KDQOL) [48], a well validated tool in kidney disease which has demonstrated good test-retest reliability on most dimensions (includes general health, activity limits, ability to accomplish desired tasks, energy level, and social activities). Symptoms and problems will also be assessed (questions 17–28) and include items about how bothered a respondent feels by sore muscles, chest pain, cramps, itchy or dry skin, shortness of breath, faintness/dizziness, lack of appetite, feeling washed out or drained, numbness in the hands or feet and nausea. Anxiety and depression will also be assessed using the KDQOL-36™ and is measured within the mental component of the tool (questions 1–12).
*EQ-5D-5L* The EQ-5D [49] is the National Institute of Health and Clinical Excellence’s (NICE) preferred method of measuring health effects in economic evaluations and it has shown to be a valid instrument for the measurement of health status in renal patients. The use of the new 5 level version, EQ-5D-5L, is also advocated by NICE. It consists of a descriptive system and a visual analogue scale. The EQ-5D-5L will be self-completed by the patients or the Research Nurse and also completed for the patient by the carer (i.e. by proxy). The inter-rater agreement can then be assessed.
*POS-S Renal* The POS-S Renal was developed in 2011 and is used as a tool to monitor progress in individual symptoms. It is a brief tool, primarily aimed at patients with advanced disease [50].
*6 Item Cognitive Impairment Test (6CIT)* The 6 Item Cognitive Impairment Test (6CIT) Kingshill Version 2000® was developed in 1983 [51] and is a useful dementia screening tool in Primary Care. The tool will be used to identify cognitive impairment and changes over time during the course of the study.
*9-point Clinical Frailty Scale* Frailty will be studied using the 9-point Clinical Frailty Scale [52]. The Clinical Frailty Scale© has performed better than measures of cognition, function or comorbidity in assessing risk for death.

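### The protocol is inconsistent on carer help with the patient's EQ-5D-5L, and nothing keeps that form independent of the same carer's proxy rating

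*Protocol article*

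**What the plan says.** In the protocol, under Recruitment, Patients (text below Fig. 1), the rule for all patient questionnaires is: "If patients wish they can complete questionnaires themselves, with the nurses or with their carers". The next sentence adds a record of the mode: "The way in which the data are captured (self-completion or help from staff member or carer) will be noted on the front sheet of the" [forms].

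Table 2, in the entry for this instrument, says something narrower: "The EQ-5D-5L will be self-completed by the patients or the Research Nurse and also completed for the patient by the carer (i.e. by proxy"). It continues: "The inter-rater agreement can then be assessed".

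The carer's proxy rating is scheduled at baseline and at every 3-monthly visit (Table 1; Data collection, Carers) and is listed as a secondary carer outcome. The proxy rater is the enrolled carer, since under Study population, Carers, "participants must identify as the primary carer for the patient who has made a confirmed decision for conservative kidney management". Carers who opt in are invited to the patient's next clinic appointment for consent and baseline data (Recruitment, Carers), which is also the visit at which the patient gives consent and baseline is set (Recruitment, Patients).

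**The concern.** An agreement statistic describes two raters only if each forms a rating without the other. Under the general rule, the primary carer may sit with the patient while the patient's EQ-5D-5L is filled in and then rate the patient on the same instrument, possibly at the same visit. For such a pair, part of the measured agreement reflects the shared sitting and not the carer's ability to judge the patient's health.

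Table 2 does not list carer help for this form, so a site cannot tell which rule applies. The choice matters when the form is completed: an analysis plan written later can leave out the affected pairs, but it cannot recover an independent rating.

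The population makes carer help plausible. The protocol expects fatigue and takes account of cognitive abilities (Study quality, monitoring and ethical considerations), and its Discussion describes a usually frail group. If help became more common as patients declined, apparent agreement could rise over the 12 months for that reason alone.

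**Working it through.** **The plan's own figures.** The protocol gives no figure for patient-proxy agreement. Its one sample-size calculation is for the mean EQ-VAS: "Using a standard deviation estimate of 18 from a similar study", with 100 evaluable patients. The 95% CI width is 2 × 1.96 × 18 / √100 = 7.06, or 7.20 with a multiplier of 2, against 7.2 stated. Inflating for 10% loss gives 100 / 0.90 = 111.1, so 112. Both figures reproduce, and neither depends on this point.

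**The texts side by side.**
- Recruitment, Patients: the patient alone, with a nurse, or with a carer; all questionnaires.
- Table 2, EQ-5D-5L: the patient or the research nurse; the carer appears only as proxy.
- No section says that the patient's form and the proxy form must be completed separately.

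**Size, on assumed inputs.** Let P be the patient's unaided score and C the carer's independent score, with equal means and equal SD (18; it cancels) and correlation ρ, which is then the true ICC. In a share f of pairs the enrolled carer helped, and the recorded patient score is R = (1 − w)P + wC, where w is the carer's influence. In units of the common variance:

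- cov(R, C) = (1 − f)ρ + f[(1 − w)ρ + w]
- var(R) = (1 − f) + f[(1 − w)² + w² + 2w(1 − w)ρ]
- pooled ICC = 2 cov(R, C) / (var(R) + 1)

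Example with ρ = 0.50, f = 0.25, w = 0.5: cov = 0.375 + 0.25 × 0.75 = 0.5625; var(R) = 0.75 + 0.25 × 0.75 = 0.9375; ICC = 1.125 / 1.9375 = 0.58.

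Pooled ICC when the true value is 0.50:

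| Share assisted f | w = 0.25 | w = 0.5 | w = 1 |
|---|---|---|---|
| 10% | 0.52 | 0.53 | 0.55 |
| 25% | 0.54 | 0.58 | 0.63 |
| 50% | 0.59 | 0.67 | 0.75 |

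A simulation of 400,000 pairs agrees with these values to within about 0.002.

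Ends of the range:
- Smallest rise (ρ = 0.60, f = 0.10, w = 0.25): cov = 0.54 + 0.10 × 0.70 = 0.61; var(R) = 0.90 + 0.10 × 0.85 = 0.985; ICC = 1.22 / 1.985 = 0.615, a rise of 0.015.
- Largest rise (ρ = 0.40, f = 0.50, w = 1): cov = 0.20 + 0.50 = 0.70; var(R) = 1; ICC = 0.70, a rise of 0.30.

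With f = 0 or w = 0 the rise is zero. If carers rate 5 points lower on average, the simulated values start lower but rise in the same way, for example from 0.482 to 0.563 at ρ = 0.50, f = 0.25, w = 0.5. Restricting to pairs without carer help returns 0.50, provided that help is unrelated to agreement.

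**The case against.** The strongest reply is that the text specific to this instrument governs. Table 2 names the patient or the research nurse, and the sentence on carer help is generic. Carer help on this form may never have been intended. Even where it happens, the carer completes the form with the patient and is not described as answering for the patient, and patients without capacity to consent are excluded. The mode of completion is recorded, so affected pairs can be identified. Agreement is not a stated objective, a listed outcome or part of the analysis sections; Table 2 says only that it can be assessed. How it is analysed may stand in an analysis plan that is not shown.

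Much of this stands. It limits the weight of the point and makes its size unknowable from the documents. It does not remove the conflict between the two places, and recording the mode does not make the ratings independent.

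A reader might also infer more than the documents support:
- **That all pairs will be pooled.** No agreement analysis is specified, so no pooling rule exists to criticise.
- **That the result decides whether proxies may replace patients.** No section plans such substitution; the proxy rating is a separate carer outcome.
- **That agreement is inflated throughout.** The bias needs the helper to be the enrolled carer and the help to move an answer. Self-completed and nurse-assisted forms are not affected in this way.
- **That postal completion offsets the bias.** The text reads "If the carer is unable to attend this clinic visit then the Research Nurse will send a consent form and baseline data collection tools" to the home. This concerns baseline only, and no different day is stated, so its effect cannot be judged.

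**Conclusion.** The point holds as an internal inconsistency with a missing safeguard. The protocol permits carer help in one place and omits it for this instrument in another, and it nowhere requires the patient's rating and the carer's proxy rating to be independent. In pairs where the enrolled carer helped, agreement will tend to be biased upward.

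The assumed inputs (true ICC 0.40 to 0.60, 10% to 50% of forms assisted, influence 0.25 to 1) give a rise of about 0.015 to 0.30. None of these inputs is in the documents, and the rise is zero if help changes no answers. The direction is better supported than the size.

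Agreement is a side analysis, so this is a minor to moderate point. The sample size is unaffected. The documents do not say that carer-assisted EQ-VAS values will be treated as self-reported in the primary mean, so for that outcome there is reason only for an optional sensitivity analysis.

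**What to change.** 1. Reconcile the text under Recruitment, Patients with the EQ-5D-5L entry in Table 2, so that both say who may help with the patient's form.
2. Instruct sites to have the patient's EQ-5D-5L and the carer's proxy EQ-5D-5L completed separately, with any help on the patient's form coming from the nurse where possible.
3. Base the agreement analysis on pairs whose patient form was self-completed or nurse-assisted, using the front-sheet record, and report carer-assisted pairs separately.
4. Optionally, show the 3-month EQ-VAS mean by mode of completion as a sensitivity analysis.

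The cost is a few sentences in the protocol, site instructions and analysis plan; no new data item is needed. The agreement analysis loses the carer-assisted pairs, so its confidence interval is somewhat wider. The retained pairs may come from fitter patients, which is why the assisted pairs should still be shown.

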#### Carers

With the patient’s agreement, and if the patient is happy for the carer to participate in the study, information will be sent to the patient to give to their carer. Carers will be asked to contact the Research Nurse if they are interested in ‘opting-in’ to the study. If a carer is interested in participating they will be invited to attend the patient’s next clinic appointment so that informed consent can be obtained and baseline data collected (see Fig. 1). If the carer is unable to attend this clinic visit then the Research Nurse will send a consent form and baseline data collection tools to their home. The carers will be asked to return the consent form to the hospital. Information on how to complete the tools will be given over the telephone. Carers can either complete the tools themselves or with the assistance of a Research Nurse.

#### Renal physicians/clinical nurse specialists

Renal physicians and CNS from each of the ten study sites who fulfil the inclusion criteria will be identified through the lead nephrologists or senior renal managers for each study site. The renal physicians and CNS will be invited to take part in a semi-structured qualitative interview, conducted to explore their experience of counselling a patient who ultimately declines dialysis (see Fig. 1). They will be approached by the Chief Investigator of the study via email. Written informed consent will be obtained prior to the interview taking place. Recruitment will continue until data are saturated [39].

#### Sample size

The primary outcome is to measure the true mean QOL at 3 months using the EQ-5D-5L Visual Analogue Scale (EQ-VAS). The EQ-VAS asks patients to place their health on an interval scale from 0–100 where 0 is the worst state they can imagine and 100 is the best. Using a standard deviation estimate of 18 from a similar study (Nephrol Dial Transplant (2004) 19: 1594–1599),with 100 individuals in our sample we would calculate a 95 % confidence interval for the true mean which would be of width 7.2 units, i.e. 95 % of the time we would estimate the true mean within plus or minus 3.6 units. With an estimated death/dropout rate at 3 months of 10 %, a total of 112 patients are required. For the exploratory qualitative interviews with nephrologists and CNS, in order to achieve data saturation when no new patterns emerge, a sample of approximately 15–20 will be recruited until data saturation reached [39].

#### User involvement

The proposal has been developed in collaboration with members of the Kidney Research and Education Initiative (KREI), established in 2010 to broaden collaborative working between renal research groups and renal education teams to ensure involvement with patients, carers, academics, clinicians and researchers [40]. In addition, we collaborated with the Northern Ireland Kidney Patient Association (a self-help group run by patients with ESKD and their carers) to help set the study aims and objectives. All those involved in this research proposal have personal knowledge and experience of kidney disease and offer differing perspectives to the research team. Regular feedback meetings will be arranged on the progress of the research for comment and scrutiny with a particular focus on ethics, documentation (for example in questionnaires, and information leaflets) and methodology. This shared decision-making will strengthen the partnership between patients, clinicians and researchers involved in the research. Several of the questionnaires were reviewed by members of the Northern Ireland Kidney Patient Association and they provided constructive feedback on feasibility of the study to the research team. The data collection tools were then piloted with 5 patients and 5 carers aged over 70 years attending a renal clinic to test for their clarity, ease of use and time burden. Minor changes were made to the tools to be used to collect economic information from patients and carers. All patients, carers, renal physicians and CNS will have the right to withdraw from the study at any time.

### Data collection

#### Patients

At baseline the research nurse will collect patient demographics through a review of clinical records at study entry (Table 1). Data collected will include age, gender, ethnicity (using UK Office for National Statistics categories), marital status, disease severity (as measured by eGFR) and primary renal disease; comorbidity using the Davies Comorbidity Score. Information will also be obtained on smoking habits of the patient, their diabetes status and on the presence or absence of vascular disease (ischaemic heart disease, angina, myocardial infarction, percutaneous coronary intervention, coronary artery bypass graft, peripheral vascular disease and cerebrovascular accidents). Biochemical data at time of entry to the study will be recorded including serum creatinine, albumin, calcium, phosphate, parathyroid hormone, alkaline phosphatase, liver function tests, haemoglobin level and urine protein creatinine ratio. The research nurse will also be asked to document a ‘Yes’ or ‘No’ answer to the question, ‘would you be surprised if the patient dies within 6 months?’ They will also complete the 9-point Clinical Frailty Scale, 6 item Cognitive Impairment Test (6CIT) and Palliative Performance Score (PPS). Detail from patients’ hospital notes will be collected on who made the decision to accept conservative management. The Decisional Conflict Scale (DCS) will be completed at baseline and 6 monthly (see Table 2).

**Table 1 Tab1:** Schedule of Assessments

Table 1	Screening	Visit (1)	Visit (2)	Visit (3)	Visit (4)
	Baseline	3 months	6 months	9 months	12 months
PATIENT					
Informed Consent	X				
Inclusion/Exclusion Criteria	X				
Demographic Data	X				
Detail from patient’s hospital notes on who made decision to accept CM	x				
Davies Comorbidity Score	x	x	x	x	x
9-point Clinical Frailty Scale	x	x	x	x	x
6 Item Cognitive Impairment Test (6CIT)	x	x	x	x	x
Functional performance using the PPS	x	x	x	x	x
KDQOL	x	x	x	x	x
EQ-5D-5L	x	x	x	x	x
POS-S Renal	x	x	x	x	x
DCS	x		x		x
Patient Service Use Log	x	x	x	x	x
Serum creatinine, albumin, calcium, phosphate, parathyroid hormone, alkaline phosphatase and haemoglobin level	x	x	x	x	x
Urine protein creatinine ratio	x	x	x	x	x
Liver function tests	x	x	x	x	x
Smoking habits of patient	x	x	x	x	x
Smoking habits of other people living in household	x	x	x	x	x
Diabetes and diabetic comorbidity check	x	x	x	x	x
Check for Ischemic heart disease, angina, myocardial infarction, percutaneous coronary Intervention, coronary artery bypass graft, peripheral vascular disease, cerebrovascular accidents in all patients.	x	x	x	x	x
Answer question ‘Would you be surprised if patient dies within 6 months?	x	x	x	x	x
CARER					
Informed Consent	x				
Inclusion/Exclusion Criteria	x				
EQ-5D-5L	x	x	x	x	x
EQ-5D-5L for the patient by the carer (i.e. by proxy)	x	x	x	x	x
DCS	x		x		x
Carer baseline questionnaire	x				
Follow up carer questionnaires		x	x	x	x
RENAL PHYSICIAN/ CLINICAL NURSE SPECIALISTS	At one point during study				
Qualitative interview

**Table 2 Tab2:** Data collection tools for PACKS study

**Tools for use with patient**
*Kidney Disease QOL-36™* Quality of life of patients will be measured using the Kidney Disease QOL-36™ Survey (KDQOL) [48], a well validated tool in kidney disease which has demonstrated good test-retest reliability on most dimensions (includes general health, activity limits, ability to accomplish desired tasks, energy level, and social activities). Symptoms and problems will also be assessed (questions 17–28) and include items about how bothered a respondent feels by sore muscles, chest pain, cramps, itchy or dry skin, shortness of breath, faintness/dizziness, lack of appetite, feeling washed out or drained, numbness in the hands or feet and nausea. Anxiety and depression will also be assessed using the KDQOL-36™ and is measured within the mental component of the tool (questions 1–12).
*EQ-5D-5L* The EQ-5D [49] is the National Institute of Health and Clinical Excellence’s (NICE) preferred method of measuring health effects in economic evaluations and it has shown to be a valid instrument for the measurement of health status in renal patients. The use of the new 5 level version, EQ-5D-5L, is also advocated by NICE. It consists of a descriptive system and a visual analogue scale. The EQ-5D-5L will be self-completed by the patients or the Research Nurse and also completed for the patient by the carer (i.e. by proxy). The inter-rater agreement can then be assessed.
*POS-S Renal* The POS-S Renal was developed in 2011 and is used as a tool to monitor progress in individual symptoms. It is a brief tool, primarily aimed at patients with advanced disease [50].
*6 Item Cognitive Impairment Test (6CIT)* The 6 Item Cognitive Impairment Test (6CIT) Kingshill Version 2000® was developed in 1983 [51] and is a useful dementia screening tool in Primary Care. The tool will be used to identify cognitive impairment and changes over time during the course of the study.
*9-point Clinical Frailty Scale* Frailty will be studied using the 9-point Clinical Frailty Scale [52]. The Clinical Frailty Scale© has performed better than measures of cognition, function or comorbidity in assessing risk for death.
*Palliative Performance Scale (PPS)* The Palliative Performance Scale [53] uses five observer-rated domains correlated to the Karnofsky Performance Scale (100–0). The PPS is a reliable and valid tool and correlates well with actual survival and median survival. It has been found useful for purposes of identifying and tracking potential care needs of palliative care patients, particularly as these needs change with disease progression.
*Decisional Conflict Scale (DCS)* This will be used to explore satisfaction with decision making from a patient perspective. The scale measures uncertainty and difficulties in the decision making process [54]. The 16 item version measures four domains: a) uncertainty in choosing options; b) unsupported in decision making; c) feeling informed; d) decision is consistent with values. The instrument demonstrates satisfactory reliability and good construct validity [55]. It has been used extensively in the United Kingdom. It will be used with patients at baseline, 6 and 12 months.
*Patient Log* Questionnaires have been developed using items from the Annotated Cost Questionnaire [56] and the iMTA Valuation of Informal Care Questionnaire [57]. These will measure healthcare resource utilisation (and associated costs) by patients.
